### 2.8. Data Collection and Assessment Plans

For the present trial, the outcomes will be measured at baseline, posttreatment, 6-month follow-up, and 1-year follow-up. Weight, body fat percentage, waist and hip circumference, and blood pressure will also be measured monthly during the intervention period (see Figure 1 for details of the assessment schedule). Self-reported measures will be collected using the *Encuesta Fácil* online platform (www.encuestafacil.com). Assessment sessions will take place in a computer room and a laboratory in the Faculty of Psychology at UPV/EHU, located in Donostia-San Sebastian. Blood samples will be collected by a nurse in each participant’s primary care unit. A nutritionist will be responsible for evaluating anthropometric and dietetic aspects, having been trained specifically for that task. A psychologist will be in charge of conducting the assessment sessions for the other variables evaluated in the study, having also been trained for that purpose. The evaluated outcomes and the properties of the assessment instruments to be used are detailed below.

#### 2.8.1. Enrollment Criteria and Baseline Characteristics

##### Demographics

Data related to the participants’ gender and age will be collected.

##### Weight-Related Information

Information will be requested about the participants’ self-reported weight and height (in order to calculate self-reported BMI and exclude those that clearly do not meet the inclusion criteria), weight history, and the existence of any excess weight-related illnesses.

##### Participation Motivation

People interested in participating in the study will be asked about their reasons for taking part, with the purpose of establishing their motivation for doing so.

#### 2.8.2. Primary Outcomes and Measures

##### Quality of Life

Quality of life will be assessed by the Spanish version of the Impact of Weight on Quality of Life-Lite Questionnaire (IWQOL-Lite) [56], an instrument that measures quality of life in people with obesity. This 31-item questionnaire comprises 5 subscales that measure weight-related concerns across 5 domains: Physical function, self-esteem, sexual life, public distress, and work. The whole scale and the 5 subscales have shown good reliability (Cronbach’s *α* = 0.88–0.95).

##### Weight Self-Stigma

Weight self-stigma will be assessed by the Spanish adaptation of the Weight Self-Stigma Questionnaire (WSSQ) [57], which is a 12-item questionnaire used to assess weight-related self-stigma in people with overweight or obesity, and, in addition to the total score, comprises the following two subscales: self-devaluation and fear of enacted stigma. The whole scale and the subscales show good internal consistency (Cronbach’s *α* = 0.81–0.88).

##### General Health

Current general health status will be assessed using the Spanish version of the General Health Questionnaire-28 (GHQ-28) [58]. In addition to the total score, this measure consists of 28 items comprising the following 4 subscales: Somatic symptoms, anxiety/insomnia, social dysfunction, and severe depression. Both the total score and subscales have shown good internal consistency (Cronbach’s *α* = 0.91–0.97) [59].

##### Eating Habits

Eating habits will be assessed by two 24-h recalls (on alternate days) and the 14-item Mediterranean Diet Assessment Tool [60], a 14-item questionnaire that evaluates adherence to the Mediterranean diet. Eating habits will be examined through the Easydiet© software package (online version 2019) developed by the Spanish Centre for Higher Studies in Nutrition and Dietetics (CESNID).

##### Physical Exercise

Physical exercise will be estimated by the Spanish short version of the International Physical Activity Questionnaire (IPAQ) [61], which is a questionnaire comprising 7 items that assess physical activity levels. This questionnaire provides information about the time an individual has spent walking, doing moderate intensity exercise, vigorous intensity exercise, and sedentary activities in the last 7 days. The short Spanish version of the questionnaire has shown very good reliability (Spearman’s *ρ* = 0.81) among the US population.

##### Eating Behavior

Eating behavior will be assessed by the Spanish version of the Dutch Eating Behavior Questionnaire (DEBQ) [62]. This comprises 33 items and 3 subscales related to various intake behaviors: Emotional, external, and restrained eating. All of its subscales have shown good internal consistency (Cronbach’s *α* = 0.84–0.94).

#### 2.8.3. Secondary Outcomes and Measures

##### BMI

Weight will be measured using a bioelectrical impedance analysis technique with a Tanita body composition monitor (Tanita Corp., Tokyo, Japan), and height will be measured using a wall-mounted stadiometer (SECA 220, Hamburg, Germany). These values will then be used to calculate BMI, and the participants will be classified as having overweight or obesity according to the IOTF cutoff points.

##### Body Fat Percentage

Body fat percentage will be estimated using a bioelectrical impedance analysis technique with a Tanita body composition monitor (Tanita Corp., Tokyo, Japan).

##### Waist and Hip Circumference

Waist and hip circumference will be measured by inelastic tape (Holtain^®^, Crymych, UK).

##### Blood Pressure

Blood pressure will be measured with a sphygmomanometer (Geratherm^®^, Geschwenda, Germany).

##### Lipid Profile

Total, LDL-, and HDL-cholesterol will be assessed with a blood test.

##### Glucose Level

Glucose levels will be measured by spectrophotometry.

##### Insulin Sensitivity

Insulin sensitivity will be measured using homeostasis model assessment (HOMA).

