The primary aim of this study is to evaluate the effectiveness of a well-being centered ACT- and mindfulness-based group intervention following the VHL perspective in conjunction with the treatment as usual (TAU) (Mind&Life intervention) in comparison with TAU alone. The measured outcomes will be quality of life, weight self-stigma, general health, eating habits, physical activity, and eating behaviors (i.e., emotional eating, restrictive eating, and external eating) of people with overweight or obesity in the short, medium, and long term. It is hypothesized that, in comparison with people receiving TAU (control group), those receiving the Mind&Life intervention (experimental group) will show a greater improvement in these outcomes in the short, medium, and long term.

A secondary goal of this study is to examine the effectiveness of the Mind&Life intervention when considering anthropometric measures (i.e., weight, body mass index (BMI)), body composition measures (i.e., body fat percentage, waist and hip circumference), cardiovascular measures (i.e., blood pressure), and physiological measures (i.e., lipid and glucose profile) at the short, medium, and long term. It is anticipated that the experimental group will show a greater improvement in these variables than the comparison group in the short, medium, and long term. In addition, this trial aims to analyze the mediating and moderating role of various process measures (i.e., psychological flexibility, weight-related psychological flexibility, mindfulness abilities, self-compassion, valued living, and cognitive fusion) in the relationship between the Mind&Life intervention and all outcome measures. We will also examine the mediating and moderating role of weight self-stigma and emotional eating in the relationship between the Mind&Life intervention and all outcome measures.

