#### 2.3.2. Sample

##### Eligibility Criteria

Participants will be eligible if they (1) have overweight or obesity (estimated by BMI ≥ 25 kg/m^2^ and classified by the International Obesity Task Force, IOTF); (2) are between 20 and 70 years old; and (3) seek weight management treatment. Participants will be excluded if they (1) have an eating disorder diagnosis such as binge eating disorder, anorexia, or bulimia; (2) have any psychiatric disorder or intellectual disability that prevents them from taking part in the intervention; or (3) have insufficient knowledge of the language in which the intervention will be implemented.

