
#### 2.4.3. Concomitant Interventions

This trial will be incompatible with receiving any kind of additional psychological or dietetic treatment. Nevertheless, drugs for controlling blood pressure, diabetes, or cholesterol will be permitted.

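### HOMA is compared in all participants although injected insulin is not ruled out, and the index does not measure insulin sensitivity in anyone who injects it

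*Protocol article*

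**What the plan says.** All references are to the protocol article.

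- **Outcome.** Section 2.8.3, Insulin Sensitivity: "Insulin sensitivity will be measured using homeostasis model assessment (HOMA"). No index (resistance or sensitivity) is named, and no participant is left out.
- **Other blood measures.** Section 2.8.3 lists cholesterol fractions ("Total, LDL-, and HDL-cholesterol will be assessed with a blood test") and glucose ("Glucose levels will be measured by spectrophotometry").
- **Permitted drugs.** Section 2.4.3: "drugs for controlling blood pressure, diabetes, or cholesterol will be permitted". No class of diabetes drug is singled out.
- **Exclusions.** Section 2.3.2 excludes people for an eating disorder, for a psychiatric disorder or intellectual disability that prevents participation, or for insufficient command of the language. Diabetes and insulin treatment do not appear.
- **Schedule and analysis.** Section 2.8 measures the outcomes before treatment, after it, and at 6 months and 1 year. Section 2.10 compares the groups on every study outcome by ANOVA or ANCOVA. A covariate is added when a variable differs at baseline, and the change from before to after treatment is added at the follow-up points.

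**The concern.** HOMA is an indirect measure. It takes fasting glucose and fasting insulin and assumes that the insulin is the person's own steady-state response to that glucose. If some of the insulin was injected, the assay value depends on dose and timing, and the index no longer describes insulin sensitivity. A drug that makes the pancreas release more insulin causes a similar but smaller distortion.

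The permitted drugs, the exclusions, the unrestricted outcome and the single analysis rule together put such a participant into the HOMA comparison like anyone else. Diabetes is foreseeable in this population: the Introduction links excess body fat to it, and section 2.4.3 provides for its treatment.

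What is at stake is the meaning of one secondary outcome. Invalid values add scatter. If medication were started, stopped or adjusted more often in one arm, the resulting shift could be read as an effect of the Mind&Life intervention on insulin sensitivity.

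**Working it through.** The article gives no figure for HOMA, so there is none to reproduce. The check has three parts.

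**1. Following the text.** Take a participant with obesity who injects insulin.
- Section 2.3.2: no exclusion criterion applies.
- Section 2.4.3: treatment for diabetes is allowed.
- Section 2.8.3: HOMA is obtained.
- Section 2.10: HOMA is analysed with all other outcomes. The covariate rule does not help. Adjusting for a baseline imbalance neither removes a value that does not measure the construct nor deals with a dose change during follow-up.

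**2. How the index responds to insulin.** The usual resistance form is

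HOMA-IR = fasting glucose (mmol/L) × fasting insulin (µU/mL) / 22.5.

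At an assumed glucose of 5.5 mmol/L:

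| Assumed insulin (µU/mL) | HOMA-IR |
|---|---|
| 5 | 5.5 × 5 / 22.5 = 1.22 |
| 10 | 5.5 × 10 / 22.5 = 2.44 |
| 20 | 5.5 × 20 / 22.5 = 4.89 |
| 40 | 5.5 × 40 / 22.5 = 9.78 |

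At fixed glucose the index is proportional to measured insulin, whatever its source.

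For the between-arm difference, suppose a share p of an arm has values displaced by an average δ. That arm's mean moves by p × δ, so the difference between arms moves by p_E × δ_E − p_C × δ_C (E experimental, C control). Under randomisation this is zero in expectation at baseline. The variance within each arm still rises, by p(1 − p)δ² if the displacement is constant and the true values are otherwise alike. Bias needs p or δ to diverge between arms later, for example through different medication changes.

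**3. Cost of restricting the analysis set.** Section 2.3.2 gives 55 per arm and 20% attrition: 55 × 0.8 = 44 completers. The share of insulin users is not stated, so a range is assumed. The detectable standardised difference d is for a two-sample t-test at two-sided 5% and 80% power.

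| Assumed share left out | Evaluable per arm | Detectable d |
|---|---|---|
| 0% | 44.0 | 0.60 |
| 2% | 44 × 0.98 = 43.1 | 0.61 |
| 5% | 44 × 0.95 = 41.8 | 0.62 |
| 10% | 44 × 0.90 = 39.6 | 0.64 |

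The restriction costs little power. The point is about validity.

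**The case against.** The strongest objection is that the document never mentions injected insulin. Such participants are possible but not shown to exist, and handling one derived secondary variable in a medicated subgroup is detail that an analysis plan may contain. The number is indeed unknown and may be zero. Even so, the article does fix an unrestricted outcome, an admitted population and one analysis for all outcomes, and these do not fit together for anyone who injects insulin.

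Two stronger readings are tempting, and the documents support neither.

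- **That HOMA cannot be calculated.** No insulin assay is listed, and the secondary aim in the Introduction speaks of "physiological measures (i.e., lipid and glucose profile) at the short, medium, and long term". A reader might infer that insulin will not be measured. But naming HOMA implies a paired fasting insulin value. The one-line entries in section 2.8.3 are not presented as a complete assay list, and section 2.8 says only "Blood samples will be collected by a nurse in each participant’s primary care unit". A condensed article commonly leaves analytes and fasting rules to the full protocol. There is no ground here for deleting the outcome.
- **That the arms will be pushed far apart.** Assume a typical HOMA-IR of 3 and two insulin users at 15 among 44 completers. The arm mean rises by 2 × (15 − 3) / 44 = 0.55, or 18% of 3. That is the mean of one arm with both users in it and none in the other. With one user in each arm, and arms of equal size, the difference between arms does not move. The figure also depends on the index: on a reciprocal scale the same values shift the mean by 2 × (1/3 − 1/15) / 44 = 0.012, or 3.6% of 1/3. It is not evidence of a between-arm effect.

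**Conclusion.** The point holds as a limited matter of validity. As written, the plan admits participants in whom HOMA does not measure insulin sensitivity and gives no restriction for them in this analysis. The expected consequence under 1:1 allocation is mainly extra noise, with possible bias if glucose-lowering medication changes differently in the two arms. The size cannot be fixed from the document, because it depends on an unstated number of users.

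The conclusion rests on how HOMA works and on the absence of any exclusion for diabetes or insulin treatment. The primary outcomes and the sample size are unaffected. This is a worthwhile improvement to one secondary outcome, not a defect that threatens the trial.

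**What to change.** 1. Name the HOMA index. Resistance and sensitivity indices run in opposite directions.
2. Analyse it on the log scale. The index is multiplicative in insulin, and the log limits the pull of extreme values. HOMA-IR and its reciprocal then differ only in sign.
3. Define the HOMA analysis set as participants not on injected insulin at baseline. This uses only information from before randomisation.
4. State in advance how values are handled when insulin is started later, with the same rule in both arms, so that exclusion after randomisation adds no bias.
5. Record glucose-lowering medication at each of the four assessments.
6. Add a sensitivity analysis that also leaves out participants who, at baseline, take drugs that stimulate insulin release.

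The cost is a few sentences, one medication item per assessment, and slightly fewer participants for this one outcome, with the small loss of power shown above. The change concerns analysis only and implies nothing about which treatments are permitted.

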#### 2.8.4. Process Outcomes and Measures

##### Experiential Avoidance

Experiential avoidance will be assessed by the Spanish version of the Acceptance and Action Questionnaire-II (AAQ-II) [63], which is a 7-item questionnaire that evaluates general experiential avoidance and psychological inflexibility. This instrument has shown good internal consistency (Cronbach’s *α* = 0.88).

##### Weight-Related Flexibility

Flexibility in relation to difficult weight-related thoughts and feelings will be assessed by the Spanish adaptation of the Acceptance and Action Questionnaire for Weight-Related Problems (AAQ-W) [64]. This is a 22-item questionnaire that evaluates the acceptance of weight-related feelings, defusion from weight-related thoughts, and the degree to which thoughts and feelings interfere with valued action. The original version of the AAQ-W has shown good internal consistency (Cronbach’s *α* = 0.86).

##### Mindfulness Abilities

Mindfulness abilities will be assessed by the Spanish version of the Five Facets Mindfulness Questionnaire (FFMQ) [65], which is a 39-item questionnaire that assesses the capacity of an individual to engage in mindfulness practice. In addition to a total score, it comprises 5 subscales referring to 5 facets of mindfulness: Observing, describing, acting with awareness, nonjudging, and nonreactivity. The FFMQ total score and the 5 subscales have shown good internal consistency (Cronbach’s *α* = 0.80–0.91).

##### Self-Compassion

Self-compassion will be assessed by the Spanish short version of the Self-Compassion Scale (SCS) [66], which is a 12-item questionnaire that evaluates the way in which an individual shows kindness and understanding toward oneself in moments of turmoil. In addition to the total score, it comprises 6 subscales that assess components of self-compassion across 3 related facets: Self-kindness/self-judgment, common humanity/isolation, and mindfulness/overidentification. The whole scale and the 6 subscales have shown adequate internal consistency (Cronbach’s *α* = 0.71–0.85).

##### Valued Life

The fit between an individual’s actual activities and their valued behavioral pattern will be measured by the Spanish adaptation of the Valued Living Questionnaire (VLQ) [67], which is a 2-part instrument used to assess valued living. In the first part, subjects rate the importance of 10 domains of living while the second part rates how consistently the individual has lived in accord with the valued behavioral pattern within each domain over the past week. The instrument has shown adequate test-retest reliability [68].

##### Cognitive Fusion

Cognitive fusion will be measured by the Spanish version of the Cognitive Fusion Questionnaire (CFQ) [69], which is a 7-item questionnaire that evaluates the extent to which an individual is psychologically entangled with and dominated by the form or content of his/her thoughts. The scale has shown good internal reliability (Cronbach’s *α* = 0.87).

### 2.9. Data Management

Upon enrollment in the study, demographic information will be entered electronically into an Excel file to which only 2 investigators will have access. Likewise, data collected at baseline, posttreatment, 6-month follow-up, and 1-year follow-up will be accessible to only 1 investigator. Informed consent sheets, questionnaires administered on paper format, blood test results, and data related to anthropometric indicators, blood pressure, and 24-h recalls will be kept in locked cabinets which can only be accessed by the same researcher, although the nutritionist will also be aware of the latter piece of information. The information stored online will be copied onto the hard disk of the project. To ensure confidentiality, pseudonymization will be used, where participants will be provided with an ID number after signing the informed consent form, which will be used for assessments. Data forms and identification information will be stored separately, and once all data have been collected, identification information will be eliminated. Participant data will be stored in a file that will be the responsibility of the University of the Basque Country (UPV/EHU). Participants will be provided with information required to access their personal data utilized in the study, and they will be informed of their rights. Data will be preserved unless the interested individual requests its suppression.

### 2.10. Data Analysis

Primary, secondary and process-outcomes will be analyzed using the statistical program SPSS version 26.0 for Windows (IBM Corp., Armonk, NY, USA). Taking into account the aims of the study, the effects of the Mind&Life program will be examined by analysis of variance (ANOVA) and/or covariance analysis (ANCOVA), with group as the independent or fixed variable (experimental or control) and all study outcomes as dependent variables. If any difference in relation to a variable exists at baseline, it will be introduced as a covariate in the analyses. Likewise, when making comparisons at follow-up points (6-month and 1-year follow-up), pretreatment–posttreatment changes will also be introduced in the analyses as covariates. To estimate effect sizes, Cohen’s *d* will be calculated where values between 0.2 and 0.4 will indicate small effects; between 0.5 and 0.7, medium effects; and above 0.8, large effects [70]. Additionally, we will use multiple regression in order to predict the variables that best explain changes in the quality-of-life criterion variable. For mediation and moderation analyses, AMOS software will be used. For each test, values of *p* ≤ 0.05 will be considered significant.

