##### Sample Size

Sample size and power estimation were calculated for 5% alpha error, a 2-tailed test, and 80% statistical power (beta error = 20%). The trial uses a comparison group and experimental group design for which pretreatment–posttreatment differences are expected to have an effect size of 0.68 (Cohen’s *d*) for quality-of-life index. The latter has been elected due to the VHL approach of Mind&Life intervention, since among all primary outcomes, quality-of-life index could best reflect values’ work impact. This effect size is based on that of a previous trial studying an acceptance, mindfulness, and compassion-based group intervention program for people struggling with weight-related issues [44]. Since dropout rates of 4–20% have previously been observed, in the present trial, the sample size and statistical power calculations are based on a 20% attrition rate. Hence, it is estimated that 55 participants per group (110 in total) will be needed to evaluate one of the main outcomes of the study, that is, quality of life.

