### 2.5. Randomization

Participants will be randomly assigned to either the experimental or the comparison group using a 1:1 allocation ratio. Blocked randomization will be used, and a computerized random sequence generator (www.random.org) will determine the sequence of each block. First, the size of the block will be established, after which a member of the research team not involved in the assessment sessions or the delivery of the treatment will write down the allocation sequence of each block on a sheet of paper which will be concealed in an opaque, sealed envelope. At the time of allocation, once participants have provided consent, the research team member in charge of the assessments and delivery of the treatment will open the corresponding envelope to reveal the allocation sequence to assign each participant to the corresponding group.

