### 2.6. Plan to Promote Participant Adherence or Retention

Given the importance of adherence to treatment and retention in the study, the following strategies will be implemented. In the first assessment session, together with providing the information sheet and informed consent form, researchers will highlight the importance of adhering to the treatment, which will also be mentioned in the first treatment session. In particular, the researchers will emphasize the benefit of attending sessions, doing homework, and practicing mindfulness, as well as recording their daily physical activity, diet, and mindfulness practice in their everyday life. Further, in order to promote adherence to treatment, the interventionists will send a message to all participants to remind them of each TAU appointment and group session with Mind&Life once they are held biweekly. Similarly, in order to favor participant retention, in each dietetic assessment session, all participants will be given oral (and written, if requested) feedback explaining their physical state and overall development (based on anthropometric indicators). Additionally, it is expected that both the interventionists and researchers will be available to be contacted by telephone or email at any time throughout the entire study period. In all cases, attendance and attrition will be recorded with the aim of eventually comparing results based on these rates.

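### Group-only ANOVA/ANCOVA at each visit, with pre-post change as a follow-up covariate, estimates the 1-year effect poorly under 20% planned attrition; one mixed model per outcome, without that covariate, is better

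*Protocol article*

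**What the plan says.** Section 2.8 states that "the outcomes will be measured at baseline, posttreatment, 6-month follow-up, and 1-year follow-up". Section 2.10 fixes the method for all of these outcomes: effects "will be examined by analysis of variance (ANOVA) and/or covariance analysis (ANCOVA), with group as the independent or fixed variable". It names neither a time factor nor a participant effect. It adds two covariate rules. A variable that differs between the arms at baseline becomes a covariate, and comparisons at the two follow-ups also adjust for the change from pretreatment to posttreatment.

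On losses, the Sample Size section says that "the sample size and statistical power calculations are based on a 20% attrition rate". Section 2.6 adds that "attendance and attrition will be recorded with the aim of eventually comparing results based on these rates". The Introduction hypothesises superiority in the short, medium and long term.

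**The concern.** The trial's intended contribution is evidence on long-term effect, so the 1-year contrast matters most, and two features of the chosen method work against it.

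- **Who is used.** A group-only ANOVA/ANCOVA at one visit drops anyone without that visit's score unless values are imputed. The change covariate also drops anyone without a posttreatment score. The posttreatment scores of people who leave later do not inform the 1-year estimate. The trial is open to participants and the arms differ greatly in intensity, so drop-out that depends on early progress, and differs by arm, is plausible.
- **What is adjusted for.** Pre-post change is measured after randomisation and is itself a result of treatment. Holding it fixed removes the part of the 1-year effect that runs through the early response.

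Comparing results by attendance or attrition does not repair either fault. It is not a randomised comparison, and attendance is out of 5 sessions under TAU but 15 + 5 = 20 under Mind&Life plus TAU.

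**Working it through.** **The plan's own figure.** Inputs from the Sample Size section are "5% alpha error, a 2-tailed test, and 80% statistical power", d = 0.68 and 20% attrition. Normal formula: n = 2(1.960 + 0.842)²/0.68² = 33.9, so 34 per group; the t-test needs 35. Inflating, 35/0.8 = 43.75, so 44 per group. The stated 55 is not reproduced, but it errs on the safe side. With 20% loss, 55 × 0.8 = 44 complete per arm, and t-test power for d = 0.68 is 88%. Power is therefore not the issue.

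**Assumptions for the 1-year contrast (none of these is in the documents).** Scores have SD 1 and higher is better. Correlations are baseline–posttreatment 0.6, baseline–1 year 0.5 and posttreatment–1 year 0.75. The true effect is 0.50 at posttreatment and at 1 year. Drop-out after posttreatment is 15% at random in Mind&Life and 20% in TAU, concentrated among poor early responders (logistic slope 1 to 3 per unit of pre-post change).

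**Step 1: no change covariate (large-sample simulation, completers only).**

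| Estimator | 1-year estimate (truth 0.50) |
|---|---|
| ANOVA | 0.42 to 0.46 |
| ANCOVA, baseline only | 0.35 to 0.42 |
| ANCOVA, baseline only, drop-out pattern reversed | 0.58 to 0.65 |
| Likelihood estimate using posttreatment scores | 0.50 |

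**Step 2: the follow-up model in section 2.10.** Its large-sample value follows directly. Let δ₁ and δ₁₂ be the effects at posttreatment and 1 year.

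- Change only: estimate = δ₁₂ − bδ₁, with b = (0.75 − 0.5)/(2 − 2 × 0.6) = 0.25/0.8 = 0.3125. This gives 0.50 − 0.3125 × 0.50 = 0.344.
- Change and baseline: b = (0.75 − 0.6 × 0.5)/(1 − 0.6²) = 0.45/0.64 = 0.703. This gives 0.50 − 0.703 × 0.50 = 0.148.

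Simulation returns the same values with and without the drop-out above (differences of 0.001 or less), because the model already conditions on what drives drop-out.

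**Step 3: sensitivity to δ₁**, with δ₁₂ kept at 0.50.

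- δ₁ = 0: both versions give 0.50, so nothing is lost.
- δ₁ = 0.68: change only gives 0.50 − 0.3125 × 0.68 = 0.29; with baseline, 0.50 − 0.703 × 0.68 = 0.02.

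**Step 4: other correlations.** Here the true effect is 0.68 at every post-baseline visit, overall drop-out after posttreatment is 20%, and the slope on pre-post change is 1. Correlations decay with visit distance (0.5 to 0.8 between adjacent visits).

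| Estimator | 1-year estimate (truth 0.68) |
|---|---|
| Completer ANOVA | 0.67 to 0.73 |
| Completer ANCOVA, baseline only | 0.66 to 0.77 |
| ANCOVA with change | 0.47 to 0.60 |
| ANCOVA with change and baseline | 0.25 to 0.51 |
| Likelihood estimate | 0.68 |

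If all visits are equally correlated (0.5 to 0.7), b for change alone is zero and that version keeps 0.68; with baseline added it gives 0.40 to 0.45.

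**Step 5: limit of the remedy.** If drop-out in Mind&Life depends on the unseen 1-year value, the likelihood estimate is also wrong: 0.77 to 0.82 against 0.68 in the decaying-correlation setting.

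**The case against.** The strongest reply has four parts.

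1. Section 2.10 does not say that analyses are separate, that only completers are used, or that imputation is ruled out. An analysis set or missing-data rule may stand in an analysis plan that is not shown. This stands: a reader might infer that only returning participants are analysed, but the article does not say so. The point therefore rests on the model that the article does choose, and the visit-by-visit reading is the natural one, not a quoted one.
2. A reader might infer that drop-out linked to early response biases the planned 1-year comparison. The documents do not support that, because the follow-up model includes pre-post change and so conditions on that driver. This also stands. The drop-out bias in step 1 applies to a version without the covariate. It does not rescue the plan, since the covariate produces its own shortfall.
3. The sizes rest on assumed correlations, drop-out and early effects. True: the drop-out shift was at most about 0.09 SD in the second set of scenarios, its direction can reverse, and in the first set it was 0.08 to 0.15 SD. The shortfall from the covariate vanishes without an early effect, and for change alone also under equal correlations.
4. A mixed model is no cure-all. It needs drop-out to depend on observed data. With post-baseline scores as outcomes, someone with none contributes nothing. The documents do not say when the 20% will be lost, and for losses before posttreatment little is gained.

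The statement in section 2.6 on comparing results by attendance and attrition belongs to the retention plan and is not presented as the missing-data method. Calling those comparisons descriptive is enough.

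**Conclusion.** The point holds in a limited form. The group-only ANOVA/ANCOVA is a poor choice for a four-visit trial that expects 20% attrition and aims at long-term effect.

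- Without the change covariate, the 1-year estimate is biased when drop-out depends on early response and the pattern differs between arms: about 0.35 to 0.42 against 0.50 under the stated assumptions, and too large if the pattern reverses.
- With the change covariate, as section 2.10 plans for follow-up, that drop-out adds nothing. The estimate is about 0.35, or 0.15 with baseline added, against 0.50, because the covariate carries part of the treatment effect. This needs an early effect, which the trial's own hypothesis predicts.

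The documents do not support the stronger readings that attrition undermines power, or that a mixed model removes drop-out bias whatever its cause. The change should be made, since long-term effectiveness is the main claim and a better analysis is available in software already named.

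**What to change.** In section 2.10, replace the ANOVA/ANCOVA comparisons by one linear mixed model per outcome (SPSS MIXED):

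- repeated outcomes: posttreatment, 6-month and 1-year scores;
- fixed effects: arm, visit, arm × visit, baseline score and baseline × visit;
- unstructured covariance across visits;
- no pre-post change covariate.

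Include every randomised participant with at least one post-baseline score, in the assigned arm and whatever the attendance. Read the arm difference at each visit from this model. State that it assumes drop-out depends only on observed data and that it recovers little for those who leave before posttreatment. Label comparisons by attendance or attrition as descriptive.

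The cost is a change of wording and slightly more modelling work. Data collection, sample size and software stay the same.
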